#### **3.3.2.6 Spot Morning Urine (Tables 3.34.1 to 3.38.3)**

Summary statistics, namely mean (sd), median, q1, q3, minimum, and maximum for Proteins, Albumin, Creatinine, Protein-to-creatinine ratio, and Albumin-to-creatinine ratio will be tabulated by nominal visit and treatment group.

#### **3.3.2.7 TKV and absolute and percent changes in TKV (Tables 3.39.1 to 3.39.3)**

Summary statistics, namely mean (sd), median, q1, q3, minimum, and maximum for TKV and TKV absolute and percent changes from baseline onward will be tabulated by nominal visit and treatment group.

#### **3.3.2.8 Height-adjusted TKV, absolute and percent changes in height-adjusted TKV (Tables 3.40.1 to 3.40.3)**

Summary statistics, namely mean (sd), median, q1, q3, minimum, and maximum for height-adjusted TKV and absolute

and percent changes in height-adjusted TKV from baseline onward will be tabulated by nominal visit and treatment group.

#### **3.3.2.9 Lipid profile (Tables 3.41.1 to 3.44.3)**

Summary statistics, namely mean (sd), median, q1, q3, minimum, and maximum for Total cholesterol, HDL cholesterol, LDL cholesterol and Triglycerides will be tabulated by nominal visit and treatment group.

#### **3.3.2.10 Hemochrome (Tables 3.45.1 to 3.49.3)**

Summary statistics, namely mean (sd), median, q1, q3, minimum, and maximum for Leukocytes, Platelets, Erythrocytes, Hemoglobin and Hematocrit will be tabulated by nominal visit and treatment group.

#### **3.3.2.11 Total slope of eGFRmdrd and eGFRckd-epi (Tables 3.50.1-3.51.3)**

The total slope of eGFRmdrd and eGFRckd-epi will be described by the slope calculated for each patient using linear regression. Relevant summary statistics and the results of the analyses will be presented in Tables 3.50.1-3.51.3.

#### **3.3.2.1 Chronic Slope of mGFR, eGFRmdrd and eGFRckd-epi (Tables 3.2, 3.52, 3.53)**

The chronic slope of mGFR, eGFRmdrd and eGFRckd-epi will be calculated from six months onward and described by the slope calculated for each patient using linear regression. Relevant summary statistics and the results of the analyses will be presented in Tables 3.2, 3.52 and 3.53.

### **3.3.3 Other Efficacy Parameters**

#### **3.3.3.1 Time to ESRD and time to doubling of Serum Creatinine or ESRD (Tables 3.53.1-3.53.2, 3.54.1-3.54.2, Figures 1 and 2)**

The time to the ESRD and the time to the composite endpoint 'doubling of serum creatinine or ESRD' will give rise to right censored data. Kaplan-Meier curves will be plotted in Figures 1 and 2 and summary statistics, including the Kaplan-Meier estimates of the proportions of patients event-free at monthly intervals, median event times and proportions of patients providing censored values, will be given in Table 3.53.1 and 3.54.1 respectively. Confidence intervals from these proportions and for the median event time calculated using Greenwood's formula will also be provided in Table 3.53.1 and 3.54.1. Cumulative event curves will be constructed using the Kaplan-Meier procedure and the Cox regression model will be used to estimate the hazard ratio for the ESRD endpoint and 'doubling of serum creatinine or ESRD' composite endpoint with the corresponding 95% CI. The model will be adjusted for age, gender and baseline serum creatinine. Participants who didn't reach the outcome of interest will be considered as right censored. Proportionality assumptions were assessed using Schoenfeld residuals. Individual patient data for the time to ESRD and time to doubling of serum creatinine or ESRD will be listed in Appendix 12 and 13

#### **3.3.3.2 Overall, Cardiovascular and Non-cardiovascular Mortality (Tables 3.55.1 to 3.57.2 and Figures 3,4 and 5)**

Time to total death, time to cardiovascular death and time to non-cardiovascular death will be analysed as time to ESRD, outlined in Section 3.3.3.1. Kaplan-Meier curves will be plotted in Figures 3,4 and 5 while Tables 3.55.1 to 3.57.2 will contain, respectively, summary statistics associated with the

Kaplan-Meier curves, and Proportional Hazards regression model fitting details. Individual patient data for the time to death, time to cardiovascular mortality and time to non-cardiovascular mortality will be listed in Appendices 14-16.

### **3.3.3.3 Incidence of Major Cardiovascular Events (Tables 3.58.1-3.58.2 and Figure 6)**

Classification of major cardiovascular events will take place at the 'blind review' stage. A "major" CV event is, by definition, a fatal or nonfatal Serious Adverse Event (SAE). Consequently, the final list of all SAEs identified for SAE reconciliation will be considered also for classifying each event as "major CV" or not. The CV events proposed as "major" will be "peripheral revascularization or amputation", including: first event of Myocardial Infarction (MI), stroke, Transitory Ischemic Attack (TIA), first hospitalisation for heart failure, unstable angina, coronary or peripheral revascularization, mesenteric infarction or amputation. "First event" is specified in order to avoid the situation of counting the patient twice for the same event. A composite endpoint of the above mentioned "major" CV events will be considered. The single components (events) will also be evaluated. Carotid stenoses or any other vascular disease that does not result in any of the above events will not be considered as major CV events, but just as vascular changes. Frequency distributions for the number of cardiovascular events per patient will be tabulated by treatment group in Table 3.58.1. The time to the first major cardiovascular event will be analysed as time to ESRD, outlined in Section 3.3.3.1. Kaplan-Meier curves will be plotted in Figure 6, while Table 3.58.2 will contain summary statistics associated with the Kaplan-Meier curves, and Proportional Hazards regression model fitting details. Individual patient data for the time to first major cardiovascular event will be listed in Appendix 17.

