## **5. BACKGROUND**

Autosomal Dominant Polycystic Kidney Disease (ADPKD), the most common hereditary cystic renal disease, has an incidence of 1 in 800 live births and account for 7-10% of patients on dialysis in developed countries (1). ADPKD shows genetic heterogeneity, with two main genes implicated, the PKD gene 1 (85%-90% of the cases) and the PKD gene 2 (10-15% of the cases) which encode for proteins polycystin 1 and polycystin 2 respectively (1,2). Clinically, ADPKD is characterized by renal and extra renal manifestations (1). In the kidneys, multiple cysts grow from distal and collecting tubular epithelial cells producing progressive renal enlargement with relatively initial stable renal functions (3). Thereafter, both tubular and secondary interstitial damage lead to faster renal loss and end-stage renal disease (ESRD) in approximately half of all patients affected in their fifth or sixth decade of life (2,4). More than 50% of the patients display hepatic cysts derived from cholangiocyte proliferation and fluid secretion (5). Pancreatic and intestinal cysts as well as increased risk of aortic aneurysms, heart-valve defects and sudden death due to rupture of intracerebral aneurysms are extra-renal manifestations, too (6). The precise molecular pathogenic mechanisms of ADPKD are not completely understood, but experimental models in renal tubular cells suggest that defect in polycystin 1 or polycystin 2 carry out to decrease intracellular calcium and increase cAMP levels changing the cell toward a proliferative and secretor phenotype (7,8,9). Cysts growth and enlargement are mainly consequence of epithelial cells proliferation and fluid chloride secretion through apical channels dependent of cAMP (10,11). Likewise, for hepatic cyst development, the proposed mechanisms are linked to abnormalities in epithelial cell proliferation and secretion in response to high intracellular cAMP concentrations secondary to polycystin defects (12). Patients with ADPKD, at similar levels of proteinuria and blood pressure control, do not seem to benefit to the same extent of ACE inhibitor therapy and have faster decline in glomerular filtration rate (GFR) compared with other chronic kidney diseases (13). Thus, in ADPKD renoprotective interventions - in addition to achieving maximal reduction of arterial blood pressure and proteinuria, and limiting the effects of other potential disease progression promoters (such as dyslipidemia, chronic hyperglycemia, or smoking) (14,15) - should also be specifically aimed to correct the dysregulation of epithelial cell growth, fluid secretion, and extracellular matrix deposition that is characteristic of this disease. Up to now, no specific therapies for ADPKD are available, but drugs like somatostatin, rapamycin, and tolvaptan targeting to growth and chloride secretions pathways are now being testing worldwide in some clinical trials (16,17). Somatostatin is an endogenous cycled polypeptide presents in two active forms (14 and 18 amino acids) with endocrine, paracrine and autocrine actions (18). The effects of somatostatin are pleiotropic depending on the tissue and the type of receptors it binds to. Five subtypes of somatostatin receptors have been described (sst1-sst5), but on the renal tubular epithelial cells, sst1 and sst2 receptors predominate. Of interest, it has been reported that somatostatin inhibits the increase in intracellular cAMP and chloride secretion induced by arginine-vasopressin hormone (AVH) in rectal glands of sharks

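### The major cardiovascular composite has no cardiovascular-death component and carries a wrong label, so a cardiovascular death outside the listed events is censored while a TIA counts

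*Supplement*

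**What the plan says.** SAP section 3.3.3.3 sits under Other Efficacy Parameters. It opens with a general definition: a major cardiovascular event "is, by definition, a fatal or nonfatal Serious Adverse Event (SAE"). It then names the events proposed as major. The sentence introduces them under the label "peripheral revascularization or amputation" and goes on to list "first event of Myocardial Infarction (MI), stroke, Transitory Ischemic Attack (TIA), first hospitalisation for heart failure, unstable angina, coronary or peripheral revascularization, mesenteric infarction", with amputation last. The composite is formed from the events just mentioned, and the single components are also to be looked at.

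A later sentence deals with other vascular findings: "Carotid stenoses or any other vascular disease that does not result in any of the above events will not be considered as major CV events". It ends by calling such findings mere vascular changes. Classification is left to blind review, working from the reconciled list of serious adverse events.

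Time to the first major event is analysed in the same way as time to ESRD. Section 3.3.3.1 describes that analysis as Kaplan-Meier curves and a Cox model, with anyone who has not reached the outcome treated as right censored. It gives no separate rule for patients who die. Section 3.3.3.2 analyses "time to cardiovascular death" as an endpoint of its own, next to overall and non-cardiovascular mortality.

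**The concern.** The opening definition allows for fatal events, but the list that follows has no death item. A cardiovascular death with no listed event before it, or as its mechanism, therefore has no place in the composite. It falls under the general censoring rule and is treated as though the patient could still have had a first event later. A TIA or an episode of unstable angina is an event, and a sudden cardiac death is not. For an endpoint called major cardiovascular events, that ordering is hard to defend.

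The gap is relevant to this population. The background section of the appended quality-of-life protocol (PARITY-02, section 5) says of the disease that "increased risk of aortic aneurysms, heart-valve defects and sudden death due to rupture of intracerebral aneurysms are extra-renal manifestations".

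The label makes matters worse. Those who classify events at blind review will work from this paragraph, and its heading phrase describes only a small part of what the composite is meant to contain. At stake is the reading of Figure 6 and Tables 3.58.1 and 3.58.2. If the arms differed in cardiovascular deaths outside the list, the composite would not show it.

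**Working it through.** The plan states no event rate, event count or power for this composite, so it has no figure to reproduce. The check is to apply the written rules to particular cases.

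**Rules used**
- Section 3.3.3.3: a major event may be fatal or nonfatal.
- Section 3.3.3.3: the composite contains the listed events.
- Section 3.3.3.3: vascular disease that leads to none of them is not a major event.
- Section 3.3.3.1: patients without the outcome are right censored.

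**Cases**
- Fatal MI, fatal stroke, fatal mesenteric infarction: each is listed and may be fatal, so each is an event.
- Death after an earlier listed event, such as a heart-failure admission: the first event has already been counted.
- TIA with full recovery, provided it is a serious adverse event: an event.
- Sudden cardiac death or fatal arrhythmia with no listed event: not in the list, so right censored at death.
- Death from aortic rupture with no listed event: not in the list, so right censored at death.
- Death from rupture of an intracerebral aneurysm: not named, but stroke is listed and not defined, so it could be classed as fatal stroke and counted. The text does not settle it.

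**The label.** It has two items, peripheral revascularisation and amputation. Both recur inside the list. Neither can stand for MI, stroke, TIA, heart failure, unstable angina or mesenteric infarction.

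**Illustration of size, on assumed rates only.** Let *l* be the yearly rate of first listed events and *d* the yearly rate of cardiovascular death with no listed event. The share of first events left out is *d*/(*l* + *d*):
- *l* = 3%, *d* = 0.5%: 0.5/3.5 = 14%
- *l* = 3%, *d* = 1%: 1/4 = 25%
- *l* = 2%, *d* = 1%: 1/3 = 33%

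Suppose further that treatment has no effect on listed events and doubles the rate of unlisted cardiovascular deaths. A composite that included those deaths would have a hazard ratio of (*l* + 2*d*)/(*l* + *d*). With *l* = 3%, that is 4/3.5 = 1.14 for *d* = 0.5% and 5/4 = 1.25 for *d* = 1%. The endpoint as listed would show 1.0. Every input here is an assumption. The figures show how the omission works and do not estimate its size in this trial.

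**The case against.** Four points can be made on the other side.

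- **The wording is less fixed than the list suggests.** The events are only proposed, classification waits for blind review, and section 1 says that the SAP itself is reviewed then. A reader might infer a closed list that bars these deaths, and the text does not go that far. This stands, but it leaves the definition open, and the reviewers would still begin from a list without a death item.
- **The exclusion sentence is not about deaths.** It begins with carotid stenosis and ends with vascular changes. A reader might take it to exclude fatal events expressly, but it is better read as setting aside asymptomatic or incidental disease. This stands. The omission follows from the list and the censoring rule without that sentence.
- **Censoring at death is not an error in itself.** It gives a cause-specific hazard for the listed events, and a hazard ratio of 1.0 in the illustration is the right answer to that narrower question. This stands as far as the Cox model goes. It does not rescue the Kaplan-Meier curve, since 1 minus Kaplan-Meier overstates cumulative incidence when deaths are censored. Nor does it explain why an endpoint said to cover fatal events should leave these deaths out.
- **Cardiovascular deaths are reported elsewhere.** Section 3.3.3.2 gives them their own curves and Cox model, and section 3.4.2 tabulates reasons for death. A reader might infer that the trial could hide an excess of cardiovascular deaths. The documents do not support that, because such an excess would appear in those analyses. They leave the content of the composite unchanged.

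**Conclusion.** The point holds within limits. Section 3.3.3.3 contradicts itself by pairing a fatal-or-nonfatal definition with a list that has no cardiovascular death, under a label that cannot describe the list. Applied as written, the plan censors a cardiovascular death that does not occur through a listed event and counts a TIA.

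Two broader readings do not stand. Not all cardiovascular deaths are lost, because those through MI, stroke or mesenteric infarction count. Nor can it be said that aneurysm deaths in general are censored: the sudden deaths that the background mentions come from intracerebral aneurysms, which could be classed as stroke. Sudden cardiac death and aortic rupture are the clear omissions.

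The consequence is confined to Figure 6 and Tables 3.58.1 and 3.58.2. The composite is among neither the primary nor the secondary objectives in section 1, and no primary conclusion depends on it. The size of the effect cannot be derived from the documents. The change should be made because it is cheap and the definition is otherwise inconsistent.

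**What to change.** Amend section 3.3.3.3 before unblinding:

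1. Delete the label over the list.
2. Define the composite as the first of: death from any cardiovascular cause (including sudden death and aneurysm rupture), MI, stroke, TIA, admission for heart failure, unstable angina, coronary revascularisation, peripheral revascularisation, mesenteric infarction, or amputation. Use the same cardiovascular/non-cardiovascular classification of deaths as section 3.3.3.2.
3. Treat non-cardiovascular death as a competing event. Estimate the hazard ratio with a cause-specific Cox model, and show cumulative incidence in Figure 6 and Table 3.58.2 in place of 1 minus Kaplan-Meier.

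The cost is a few sentences in the SAP. Death dates are on the case report form (study-drug discontinuation and trial-end forms). Those forms show no dedicated field for cause of death, so each cause has to be classified at blind review, but sections 3.3.3.2 and 3.4.2 already require that. The one drawback is that cardiovascular death will then appear both inside the composite and as an endpoint of its own, and the report should say so.

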### 3.4 SAFETY ANALYSIS

All safety analyses will be performed using the Safety Set

#### 3.4.1 Adverse Events (Tables 4.1 to 4.5)

Adverse events with an onset after the 1st drug intake will be coded using the MedDRA classification system. Multiple reports of the same event by the same patient will be counted only once for the purposes of summary. This 'composite' event will have the 'worst' aspects of the observed multiple reports attributed to it. In particular, the worst maximum intensity, the most likely relationship to study medication and the most serious of the observed multiple reports will be attributed to the composite report. Also, if any of the multiple reports led to study drug discontinuation, this will be attributed to the composite report. This same approach will be used within a defined time period of the study, when summary of adverse events within sub-periods is undertaken. Missing values for dates will be imputed in the following way: '1' for day missing, 'January' for month missing. If however the year is missing this date will be considered as missing.

All adverse event summaries will be presented by treatment group and overall.

An overall summary of adverse events will be provided in Tables 4.1-4.5. This table will provide information on the numbers and percentages of patients with adverse events, serious adverse events, non-serious adverse events, severe adverse events, adverse events considered by the investigator to be probably related to the study drug and adverse events leading to permanent discontinuation. In addition, this table will show the average number of adverse events per patient, the average number of adverse events per patient experiencing adverse events and the number of deaths. A similar summary will be provided in Table 4.4 for serious adverse events only.

Adverse events (MedDRA preferred term) will be summarised by body system in Table 4.3. Similar summaries will be provided in Tables 4.4 to 4.5 for serious adverse events and deaths. Within the text of the statistical report, a summary of serious adverse events will be presented by treatment group, classifying whether each serious adverse event was:

- life-threatening
- permanently disabling
- required / prolonged hospitalisation
- cancer, congenital anomaly, result of overdose

Individual patient adverse event data will be listed in Appendix 18.

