**INTRODUCTION**

---

This study is a multi-centre, prospective, randomised double-blind parallel-group comparison of long acting somatostatin analogue (Octreotide LAR) and placebo.

The study is coordinated by the Clinical Research Center for Rare Diseases of the Mario Negri Institute for Pharmacological Research, Ranica, Bergamo and will be conducted with the cooperation of:

- Hospital '*Ospedale San Giovanni di Dio*', Agrigento, Italy;
- Clinical Research Center for Rare Diseases '*Aldo e Cele Daccò*', Ranica (Bergamo), Italy
- Hospital '*Ospedale Vito Fazzi*', Lecce, Italy
- Hospital '*Ospedale Maggiore Policlinico, Mangiagalli e Regina Elena*', Milan, Italy
- University '*Università Federico II*', Naples, Italy
- Hospital '*Ospedale Ca' Foncello*', Treviso, Italy

Eligible patients will be stratified for the presence (YES or NO) of concomitant clinical conditions that could appreciably affect the rate of renal function loss over time including diabetes mellitus, 24 hour urinary protein excretion >1g, or any other evidence of concomitant renal disease without indication for specific therapy. Within each stratum patients will be randomized on a 1:1 basis to Long-acting Somatostatin (Octreotide LAR) 40 mg (treatment group) or saline solution (placebo group). Data will be collected by means of an *ad-hoc* study Case Report Form (see Appendix 1).

The general aim of the trial is to assess the efficacy of one year treatment with long-acting somatostatin analogue (Octreotide LAR) compared with placebo in slowing kidney and liver growth rate in patients with ADPKD and moderate/severe renal insufficiency (estimated GFR by MDRD 4 variables: 15-40 ml/min/1.73m^2) and to assess whether and to which extent this translates into slower renal function decline over 3-year follow-up.

Primary objectives are the followings: to compare the effect of long acting somatostatin analogue (Octreotide LAR) versus placebo on total kidney volume (TKV) change (delta TKV) as assessed by spiral computed tomography (spiral CT)

scan (short-term, one year) and to compare the effect of long-acting somatostatin analogue (Octreotide LAR) vs. placebo on the rate of GFR decline as assessed by serial measurements of the iohexol plasma clearance (long-term, three years).

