| •                                                     |                |          |          |
| •                                                     |                |          |          |
| •                                                     |                |          |          |
| At 6 monthly intervals until final (at least 3 years) |                |          |          |

TABLE 1.3

REASONS FOR WITHDRAWAL

|                           | Octreotide-LAR Placebo |          | Total    |
|---------------------------|------------------------|----------|----------|
| Number of Patients        | xx                     | xx       | xx       |
| ESRD                      | xx (xx%)               | xx (xx%) | xx (xx%) |
| Unsatisfactory efficacy   | xx (xx%)               | xx (xx%) | xx (xx%) |
| Unsatisfactory compliance | xx (xx%)               | xx (xx%) | xx (xx%) |
| Protocol violation        | xx (xx%)               | xx (xx%) | xx (xx%) |
| Lost to follow-up         | xx (xx%)               | xx (xx%) | xx (xx%) |
| Withdrawal of consent     | xx (xx%)               | xx (xx%) | xx (xx%) |
| Adverse event             | xx (xx%)               | xx (xx%) | xx (xx%) |
| Death                     | xx (xx%)               | xx (xx%) | xx (xx%) |

Population: Full Analysis Set

TABLE 1.4.1

MAJOR PROTOCOL VIOLATIONS

|                               | Octreotide-LAR Placebo |          | Total    |
|-------------------------------|------------------------|----------|----------|
| Number of Patients            | xx                     | xx       | xx       |
| Major protocol violation N. 1 | xx (xx%)               | xx (xx%) | xx (xx%) |
| ...                           | xx (xx%)               | xx (xx%) | xx (xx%) |
| ...                           | xx (xx%)               | xx (xx%) | xx (xx%) |
| ...                           | xx (xx%)               | xx (xx%) | xx (xx%) |
| ...                           | xx (xx%)               | xx (xx%) | xx (xx%) |
| ...                           | xx (xx%)               | xx (xx%) | xx (xx%) |
| ...                           | xx (xx%)               | xx (xx%) | xx (xx%) |
| Major protocol violation N. n | xx (xx%)               | xx (xx%) | xx (xx%) |

Population: Full Analysis Set

TABLE 1.4.2

MINOR PROTOCOL VIOLATIONS

|                               | Octreotide-LAR Placebo |          | Total    |
|-------------------------------|------------------------|----------|----------|

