**SUMMARY OF ADVERSE EVENTS**

|                                                                               | Octreotide-LAR | Placebo   |
|-------------------------------------------------------------------------------|----------------|-----------|
| Number of Patients                                                     | xx      | xx |
| No (%) of patients with an adverse event                                      | xx (xx%)       | xx (xx%)  |
| No (%) of patients with a serious adverse event                               | xx (xx%)       | xx (xx%)  |
| No (%) of patients with a non -serious adverse event                          | xx (xx%)       | xx (xx%)  |
| No (%) of patients with a severe adverse event                                | xx (xx%)       | xx (xx%)  |
| No (%) of patients with an event probably related to study drug               | xx (xx%)       | xx (xx%)  |
| No (%) of patients with an adverse event leading to permanent discontinuation | xx (xx%)       | xx (xx%)  |
| Average number of events per patient                                          | xx.x           | xx.x      |
| Average number of events per patient (with a least 1 event)                   | xx.x           | xx.x      |
| No (%) of deaths                                                              | xx (xx%)       | xx (xx%)  |

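### The adverse-event tables carry no time at risk, so if length of observation differs by arm, the crude figures mix risk with follow-up time

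*Supplement*

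**What the plan says.** SAP section 3.4.1 describes the overall summary in terms of patients affected: "This table will provide information on the numbers and percentages of patients with adverse events, serious adverse events, non-serious adverse events". It adds "the average number of adverse events per patient" and the same average among patients who had at least one event. The template for Table 4.1 follows this, with rows for "Average number of events per patient" and for the average restricted to patients with an event. Tables 4.2 to 4.4 likewise hold counts, percentages or averages. None has a row or column for patient-years, an incidence rate or time to first event.

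Two further statements in 3.4.1 matter here. The first is a counting rule: "Multiple reports of the same event by the same patient will be counted only once for the purposes of summary". The second is a passing reference to the same approach applying "when summary of adverse events within sub-periods is undertaken". No sub-periods, tables or denominators are defined for it.

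On follow-up, the template for Table 1.3, "REASONS FOR WITHDRAWAL", lists ESRD first, with adverse event and death further down. The trial-end form records a dialysis date beside the date and reason of discontinuation. The Introduction sets entry at an estimated GFR of 15-40 and gives the long-term aim as "to assess whether and to which extent this translates into slower renal function decline over 3-year follow-up".

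Sections 3.3.3.2 and 3.3.3.3 plan Kaplan-Meier and Cox analyses for deaths and for first major cardiovascular events, which are serious adverse events by definition.

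**The concern.** A crude percentage or an average per patient compares risk between arms only if both arms are observed for about the same time. Here the effect under test could itself change how long patients are observed. If octreotide delays ESRD, and ESRD takes patients out of observation, octreotide patients accumulate more events at an unchanged rate. If octreotide patients leave sooner, for example through intolerance, the same measures understate their risk.

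What is at stake is the reading of the general adverse-event and serious-adverse-event comparison. The tables as planned would not let a reader tell a difference in risk from a difference in observation time. Total patient-years per arm, which would show whether there is a problem at all, is not planned either.

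**Working it through.** **Inputs.** Follow-up of 3 years and 1:1 allocation come from the Introduction. The documents give no exit rate, ESRD rate or adverse-event rate, so there is no planned figure to reproduce. Everything below is an assumption shown as a range: constant exit hazard h, observation ending at exit, and the same constant event rate L in both arms.

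**Step 1: mean follow-up.** For a 3-year exit probability p, h = -ln(1-p)/3 and mean follow-up is (1-exp(-3h))/h = p/h. If every occurrence is counted, events per patient are L times mean follow-up, so the ratio between arms is the ratio of follow-up times.

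| 3-year exits, placebo vs octreotide | Mean follow-up (years) | Ratio |
|---|---|---|
| equal | equal | 1.00 |
| 10% vs 8.1% (hazard ratio 0.8) | 2.85 vs 2.88 | 1.01 |
| 25% vs 15% | 2.61 vs 2.77 | 1.06 |
| 35% vs 20% | 2.44 vs 2.69 | 1.10 |
| 50% vs 30% | 2.16 vs 2.52 | 1.17 |

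If the arms are swapped, so that octreotide patients leave sooner, the ratios invert: 1/1.062 = 0.94 for 25% vs 15%, and 1/1.166 = 0.86 for 50% vs 30%.

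**Step 2: apply the count-once rule.** Section 3.4.1 counts each event once per patient, so a type of event contributes at most one. The chance that a patient contributes it is P = L/(L+h) x (1-exp(-3(L+h))). The same formula gives the crude percentage of patients with an event.

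| Exits | L = 0.1/year | L = 1/year | L = 2/year |
|---|---|---|---|
| 25% vs 15% | 22.7% vs 24.0%, ratio 1.059 | 87.8% vs 90.9%, ratio 1.034 | ratio 1.020 |
| 50% vs 30% | 19.0% vs 22.0%, ratio 1.156 | 79.2% vs 86.3%, ratio 1.089 | ratio 1.052 |

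The Step 1 ratios are therefore upper limits, approached only for rare events. Under the plan's own rule the inflation is 2.0% to 5.9% in the milder scenario and 5.2% to 15.6% in the strongest.

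**Step 3: which denominator removes it.**

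- *Counted-once events over total patient-years.* The ratio at equal risk is P1/P0 divided by the follow-up ratio. For 25% vs 15% and L = 0.1 this is 1.059/1.062 = 0.997. For 50% vs 30% and L = 2 it is 1.052/1.166 = 0.90. The longer-observed arm now looks safer than it is.
- *Patients with a first event over time at risk.* Mean time to first event or exit is (1-exp(-3(L+h)))/(L+h), and P divided by this is exactly L. For L = 0.3 and 50% vs 30%: 0.450/1.500 = 0.300 and 0.512/1.708 = 0.300. The ratio is 1.00 in every scenario.

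**The case against.** The strongest reply has four parts.

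*The premise is inferred.* A reader might infer from Table 1.3 that ESRD ends adverse-event follow-up. No sentence says so. The dialysis date also appears on the form for permanent drug discontinuation, and the main-trial protocol, where collection rules usually sit, is not shown. This stands, and the point has to be conditional. If collection continues after ESRD, that route closes, but loss to follow-up, withdrawal of consent and withdrawal for adverse events can still differ by arm.

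*The plan does handle censoring.* A reader might infer that no safety outcome accounts for time. That would be wrong: deaths and first major cardiovascular events do. The gap is confined to the general adverse-event tables. The undefined sub-period summaries do not fill it.

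*The size depends on strong scenarios.* The exits in Step 1 that give 6% to 17% imply an all-cause exit hazard ratio of roughly 0.5 to 0.6, and nothing in the documents supports so large an effect. A reader should not take 17% as the expected distortion. With a modest effect it is near 1%, and the count-once rule lowers it further.

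*The tables are descriptive.* No test between arms is planned, and individual events are listed in Appendix 18. This limits the consequences. Readers will still compare the two columns, and the tables give them no means of allowing for observation time.

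**Conclusion.** The point holds in conditional form and is a minor improvement. As written, section 3.4.1 and Tables 4.1-4.4 would mix risk with length of observation whenever adverse-event observation differs by arm, and they would not show whether it did. At equal risk, and under constant rates, the distortion is zero for equal exits and about 1% for a small difference. For assumed exits of 25% vs 15% up to 50% vs 30% it is at most 6% to 17%, or about 2-6% to 5-16% once each event is counted once per patient. Its direction depends on which arm stays longer.

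The documents do not establish that observation ends at ESRD, that exits will differ, or that the drug will delay ESRD. The finding is that the plan has no protection if they do.

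**What to change.** Keep the crude counts and percentages. Add to Tables 4.1-4.4:

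- total patient-years of adverse-event observation per arm;
- patients with a first event per 100 patient-years at risk, with time running from first study-drug intake to the first event or, without one, to the last date on which adverse events were collected.

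Base between-arm statements on these first-event rates. State in section 3.4.1 when adverse-event observation ends, in particular whether it continues after ESRD or after study drug is stopped.

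If events per 100 patient-years are also shown, count every occurrence for that column. Dividing the counted-once composite of section 3.4.1 by total patient-years would favour the longer-observed arm (Step 3).

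The cost is slightly longer tables and some derivation. Injection dates, event onset dates and discontinuation dates are already on the case report forms. The trial-end form lists no completion date, so the end of observation for completers must be taken from the last visit date. No new visits or data are needed.
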